## Abstract

Most aging populations report chronic illnesses, which are usually permanent or recurrent, significantly affect well-being and quality of life, require daily and consistent healthcare management, and last more than three months. Improved health outcomes and reduced healthcare costs are associated with self-care in treating chronic illnesses. The aim is to describe a protocol using a self-care intervention in a person with a chronic disease. A longitudinal study will be conducted with 40 patients. This article describes a protocol for a self-care intervention in a person with a chronic disease. The outcome measures will be compared with measures after the intervention in three different chronologic times. Randomization will be used to assign participants to the intervention group. The present study is expected to generate significant information about the role of self-care intervention in persons with chronic disease.

Specifications table

**Table utbl0001:** 

Subject area	Medicine and Dentistry
More specific subject area	Lifestyles and health care; Health policies and research in health services; Research in patient-centered care
Name of your protocol	SELF-CARE IN THE PERSON WITH CHRONIC DISEASE
Reagents/tools	SELF-CARE OF CHRONIC ILLNESS INVENTORY WHOQOL-BREF(PT) CORE SET
Experimental design	A quantitative longitudinal study with 400 patients randomly selected. A protocol using a self-care intervention with adults registered in consultations of diabetes, pulmonology, and cardiology who have more than one chronic disease in the Hospital. In two different chronologic times, baseline measures will be compared with measures after self-care intervention. Participants' randomization will be determined to assign them to the intervention group.
Trial registration	The study protocol was registered in the Clinicaltrials.gov NCT06235593
Ethics	The study protocol was submitted to the Research Ethics Committee of the University and Hospital and approved under No. 20/23
Value of the protocol	• This protocol is essential to determine the nursing care needs of the elderly population sample according to the self-care deficits identified in the elderly population living in their own homes or the homes of relatives or friends in the district of Évora. • There needs to be more knowledge about the effects of self-care interventions. • This article is essential to contribute to the recommendations for self-care for older adults.

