## Objectives

### Primary objectives

-To analyze the effects of a self-care intervention managed by nurses on the self-management of chronic diseases.

Secondary objectives-To characterize how a specialized intervention can contribute to changes in lifestyles, increased well-being and self-care of patients with chronic diseases.-To promote self-care maintenance, monitoring and management.

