### Outcomes and variables

Immediately after recruitment, all enrolled patients who agree to participate will sign the informed consent.

The subjects then proceed to the baseline data collection, intervention protocol, and final assessments (Fig. 1).

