**Fig. 1 fig0001:**
[figure not shown]
Intervention schedule.

In the first contact, we evaluated functionality, health-related quality of life, and Self-Care of Chronic Illness Inventory—Patient Version, with three linked sequential behaviors captured in the critical concepts of self-care maintenance, monitoring, and management. Self-care maintenance addresses behaviors patients with a chronic illness use to maintain physical and emotional stability (e.g., medication adherence). In contrast, self-care monitoring involves observing oneself for signs and symptoms (e.g., checking blood pressure): self-care monitoring links or bridges between self-care maintenance and self-care management.

We will conduct a mixed methods evaluation, including a quantitative outcome evaluation to assess the effectiveness of the intervention and a qualitative and quantitative process evaluation to derive indications for future implementation in different clinical settings (Table 1).-Anthropometry: Weight evaluation will be done using a scale and height of a stadiometer. The International Society for the Advancement of Kinanthropometry (ISAK) protocol assessed waist circumference.-Chronic diseases will be evaluated based on the number, medication and measure evaluation.-``Self-Care of Chronic Illness Inventory - Patient Version'' (version 4) instrument which includes 20 items across three scales: (i) Self-Care Maintenance (8 items); (ii) Self-Care Monitoring (6 items); and (ii) Self-Care Management (6 items). All the responses are based on a 5-point Likert scale, with one being ``Never'' or ``Not Likely'' and five being ``Always'' or ``Very Likely'' [2];-The ``WHOQOL-BREF(PT)'' instrument, which comprises 24 facets (one item per facet) clustered into four domains, allows for the measurement of the quality of life of people following the World Health Organization criteria [4].-The ``CORE SET'' (version 4) instrument, the Elderly Nursing Core Set'', aims to classify the degree of elderly functioning, which is also capable of even establishing elderly ``nursing care needs'' [5,6].

**Table 1 tbl0001:** Measures and outcomes.

Measures and outcomes	Tools of assessment	Data source
Sociodemographic data	• Sociodemographic profile	- Sex, age, educational level
Anthropometric	• Weight scale • Stadiometer • Abdominal measuring tape • Body mass index	- Weight - Height - Abdominal circumference

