## Statistical methods

Several statistical analysis techniques will be used: psychometric, descriptive, and inferential. Confirmatory Factor Analysis techniques (application of Structural Equation Models), Multiple Linear Regression Methods and Ordinal Regression Methods will also be used. A confidence level of 95 % and an error of 4.5 % will be considered.

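### Randomisation is announced, but no comparator is named and the only stated comparison is before versus after, which cannot support the claimed intervention effect

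*Protocol article*

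**What the plan says.** All places are in the protocol article.

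- **Aim.** The primary objective is "To analyze the effects of a self-care intervention managed by nurses on the self-management of chronic diseases". Under Outcomes and variables the article promises a mixed-methods evaluation, "including a quantitative outcome evaluation to assess the effectiveness of the intervention".
- **Randomisation.** Abstract: "Randomization will be used to assign participants to the intervention group". Specifications table, Experimental design row: "Participants' randomization will be determined to assign them to the intervention group". The same row also says that the patients are selected at random.
- **Comparison.** Specifications table: "baseline measures will be compared with measures after self-care intervention". Abstract: "The outcome measures will be compared with measures after the intervention in three different chronologic times".
- **Participant flow.** Outcomes and variables: "The subjects then proceed to the baseline data collection, intervention protocol, and final assessments". This sentence points to Fig. 1, which is not reproduced in the text at hand.
- **Hint of a second group.** The Intervention description says the specialist nurse informs patients in the intervention group, which suggests that some patients are not in it.
- **Design label and timing.** Study design calls the study longitudinal and prospective. Evaluation and Table 3 give a baseline assessment and assessments one and four months after the intervention.
- **Analysis.** Statistical methods lists families of techniques, for example "Multiple Linear Regression Methods and Ordinal Regression Methods will also be used". It names no between-group contrast.

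**The concern.** Randomising to an intervention group implies another group, and the value of randomisation lies in comparing the two. The article states that participants are randomised but fixes a contrast within the person, from baseline to after the intervention. Any randomisation plays no part in that contrast.

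A before-after change mixes the effect of the nurse-led sessions with everything else that moves the scores. Here that includes regression to the mean, continuing care in the diabetes, pulmonology and cardiology consultations, and answering the same questionnaires three times. Recovery is also possible, because eligibility criterion (iv), though unclearly worded, mentions patients who are sick or in hospital for acute, short-term needs.

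If scores rise for any of these reasons, the planned comparison would report an effect where there is none. A reader also cannot tell whether this is a randomised trial or a single-arm study, and the two support different conclusions.

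**Working it through.** **1. The statements side by side**

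| Question | For two groups | For one group |
|---|---|---|
| Assignment | Abstract and specifications table: randomised to the intervention group | Specifications table: patients selected at random; Study design: longitudinal and prospective only |
| Who receives it | Intervention description: patients in the intervention group | Outcomes and variables: subjects go from baseline to intervention to final assessment, no branch described |
| Comparator, ratio | None stated | – |
| Contrast | None stated | Abstract and specifications table: before versus after |
| Visit timing | – | Evaluation and Table 3: follow-up counted from the intervention |

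The text does not settle which design is meant. On either design, the stated contrast is before versus after.

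**2. Sample size used**

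Sample size calculation gives 33 cases and, with 20% dropout, 40 patients. The last step reproduces as 33 × 1.2 = 39.6, rounded to 40. The 33 cannot be reproduced, because the effect size, number of predictors and sidedness are not given. Forty patients with 20% dropout leave 40 × 0.8 = 32 completers. (The specifications table says 400 patients; I use the 40 of the Abstract and Sample size calculation.)

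**3. How often the before-after test is significant when the intervention does nothing**

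From the documents: alpha 0.05 and 32 completers. Assumed, because the documents give neither: a background improvement δ in SD units, and a baseline-to-follow-up correlation r of 0.5 to 0.7. The test is taken as a two-sided paired t-test with equal SDs at both times.

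- SD of the change = √(2(1 − r)): 1.000 at r = 0.5 and 0.775 at r = 0.7.
- Standardised drift d = δ / √(2(1 − r)).
- Noncentrality = d × √32, with 31 degrees of freedom and critical value 2.040.

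Example: δ = 0.3 and r = 0.7 give d = 0.387, noncentrality 2.19 and rejection probability 0.565.

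| δ (SD) | r = 0.5 | r = 0.7 |
|---|---|---|
| 0 | 0.050 | 0.050 |
| 0.1 | 0.085 | 0.109 |
| 0.2 | 0.195 | 0.293 |
| 0.3 | 0.376 | 0.565 |
| 0.5 | 0.782 | 0.943 |

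**4. What 40 patients deliver if there is a control arm**

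Assume 1:1 allocation, a two-sided alpha of 0.05, 80% power and a two-sample t-test.

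- 20 versus 20 (no dropout): detectable difference 0.91 SD.
- 16 versus 16 (after 20% dropout): detectable difference 1.02 SD.
- 16 versus 16 adjusted for baseline: 1.02 × √(1 − r²), which is 0.89 SD at r = 0.5 and 0.73 SD at r = 0.7.

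**The case against.** **It may be a single-arm study.** The specifications table speaks of random selection, Sample size calculation says patients come from the hospital database and calls the study explorative, and Study design mentions no parallel group. Randomisation may then loosely mean random sampling. This stands as a possible reading. On it, no randomisation is wasted and the randomisation wording is wrong, but the before-after contrast still cannot support statements about effects or effectiveness.

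**The full protocol or analysis plan may name a control arm.** It may, and then the effect could be estimated. But the article does not leave the contrast open: it states a within-person comparison in two places. A reader might infer that this study cannot estimate the effect under any circumstances. The documents do not support that; the limit applies to the comparison as written.

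**Not everyone need receive the intervention.** A reader might infer from Outcomes and variables that all enrolled patients do. The reference to all enrolled patients belongs to the sentence on consent, the flow sentence speaks only of the subjects, and Fig. 1 cannot be checked. What can be said is that this flow conflicts with the Abstract, the specifications table and the Intervention description.

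**The regression models are not shown to be invalid.** A reader might infer that linear and ordinal regression would treat the three evaluations as independent rows. Statistical methods does not say how the visits enter the models. A regression of a follow-up score on group and baseline has one row per patient and is valid. This is no part of the point.

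**The drift is assumed.** That is so. At 0.1 SD the excess over 5% is small, which is why the whole range is shown.

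**Conclusion.** The point holds. Randomisation is stated twice without a comparator or allocation, the participant flow conflicts with the Intervention description, and the only stated comparison is before versus after. That comparison cannot carry the primary objective or the promised evaluation of effectiveness. This follows from the wording alone and depends on no assumed number.

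The size of the risk does depend on assumptions. It runs from about 9% false-positive studies (drift 0.1 SD, r = 0.5) to about 94% (drift 0.5 SD, r = 0.7), against a nominal 5%. The documents do not say where in that range the study would fall. The matter should be settled before any result is reported as an effect of the intervention.

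**What to change.** Reconcile the Abstract, the Experimental design row of the specifications table, Outcomes and variables and the Intervention description, so that all describe the same design.

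- **If there is a control arm:** name the comparator condition and the allocation. Make the baseline-adjusted difference between arms, analysed by allocated group, the primary analysis. Report before-after change as descriptive only. Restate what the sample size delivers for that contrast.
- **If the study is single-arm:** delete the randomisation statements, describe how patients are sampled, and limit the objectives and conclusions to change over time, without claims of effects or effectiveness.

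The edits are to wording, but they have a price. With a control arm, the stated precision becomes less favourable: on the 1:1 assumption, only differences of about 1.02 SD unadjusted, or roughly 0.7 to 0.9 SD with baseline adjustment, are detectable with 80% power after dropout. Aiming at a smaller difference would need more patients. In a single-arm study, the conclusion becomes weaker.

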## Description of protocol

Chronic diseases affect at least 59 % of the Portuguese population. About 18 % of users of the National Health System have one chronic disease, 11 % have two, 8 % have three, and 22 % have four or more chronic diseases. Multimorbidity increases with age, so a continuous and accessible care model is essential for elderly individuals. Self-care behavior is crucial for improved health-related quality of life, and the self-care process involves maintenance, monitoring, and management [1]. The ``Self-Care of Chronic Illness Inventory—Patient Version'' is a generic measure designed to assess the self-care process. Overall, managing chronic conditions through self-care is critical in reducing healthcare costs. [2].

According to Barbara Riegel et al., self-care is essential in aging, mainly when changes occur in the person's health condition. Theoretically, this process involves three linked sequential behaviors captured in the critical concepts of self-care maintenance, self-care monitoring, and self-care management. Self-care maintenance addresses behaviors patients with a chronic illness use to maintain physical and emotional stability (e.g., medication adherence). In contrast, self-care monitoring involves observing oneself for signs and symptoms (e.g., checking blood pressure): self-care monitoring links or bridges between self-care maintenance and self-care management. A core goal of self-care monitoring is symptom recognition; once recognized, self-care management (e.g., taking medicine for a symptom) can occur, with behaviors that reflect a response to the symptoms observed. There are two approaches to measure self-care: generic and disease specific. Generic measures are applicable to a wide range of patients, while disease-specific measures are useful in specific groups with a single condition. Disease-specific measures are more responsive because they target issues experienced by patients with a specific condition. In contrast, generic measures allow comparison among patients with different conditions and accommodate those with more than one diagnosis [3].

## Objectives

### Primary objectives

-To analyze the effects of a self-care intervention managed by nurses on the self-management of chronic diseases.

Secondary objectives-To characterize how a specialized intervention can contribute to changes in lifestyles, increased well-being and self-care of patients with chronic diseases.-To promote self-care maintenance, monitoring and management.

### Study design

We have designed a longitudinal and prospective study to evaluate an intervention's effects on patients with chronic disease in a Hospital on Portugal. During the medical consultation, the patients will be invited to participate in the study and will receive a free and detailed consent form to sign if they agree to participate. We have followed the SPIRIT 2013 recommendations to ensure that our study protocol is rigorous and comprehensive.

### Subjects

Participants will be selected from the patients registered in consultations of diabetes, pulmonology, and cardiology who have more than one chronic disease in the Hospital.

### Eligibility criteria

The inclusion criteria were: individuals who (i) are aged 65 or older; (ii) are interested in participating in the project; (iii) are residing in the Évora district in their own homes or at family members' or friends' homes; (iv) patients who are sick or are hospitalized due to acute, short-term health needs, make their own decisions; and (v) present at least one chronic disease.

### Sample size calculation

Considering the explorative nature of the study, a formal sample size analysis is not possible. However, we expected to collect 40 patients, selected from the hospital database based on the G*Power software. The number of participants was calculated as 33 cases by using linear multiple regression with *α* = 0.05 and 1 − *β* = 0.80. Considering a dropout rate of 20 %, the minimum sample size was therefore derived as 40 patients.

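### The stated minimum of 40 patients misses its own target of 33 completers by one at 20% dropout, and the 80% power is not tied to the intervention effect

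*Protocol article*

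**What the plan says.** The protocol article justifies its size only under Sample size calculation. That section makes three statements.

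- Because the study is exploratory, "a formal sample size analysis is not possible".
- A calculation was nevertheless done in G*Power: "The number of participants was calculated as 33 cases by using linear multiple regression with" alpha = 0.05 and 1 − β = 0.80.
- With 20% dropout allowed for, "the minimum sample size was therefore derived as 40 patients".

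The section does not name the regression term tested, the outcome, or the comparison to which the 80% applies. The primary objective is "To analyze the effects of a self-care intervention managed by nurses on the self-management of chronic diseases". The Abstract adds: "Randomization will be used to assign participants to the intervention group". The Statistical methods section lists multiple linear regression among several techniques and does not connect it to the intervention effect.

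**The concern.** Two things look wrong.

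1. A figure called a minimum should still meet the requirement after the assumed losses. Here 20% off 40 leaves fewer than 33.
2. The section disclaims a formal calculation and then reports one, with a power figure that a reader will naturally attach to the primary objective. Nothing in the article makes that connection.

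The stake in the first is slight: one completer. The second matters more for interpretation. If the final report repeats 80% power without qualification, a null result for the intervention could be taken as coming from a study sized to detect that effect, which the article does not show.

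**Working it through.** **Inputs from Sample size calculation:** 33 evaluable cases, alpha 0.05, power 0.80, dropout 20%, 40 enrolled. **Not given there:** effect size f², number of predictors, term tested, sidedness. **Not given in the article:** comparator and allocation ratio. Anything that needs these is marked as an assumption.

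**1. Reproducing the 40.** n × (1 + d) = 33 × 1.2 = 39.6, rounded up to 40. This matches the article exactly.

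**2. Number that keeps 33 after 20% loss.** n/(1 − d) = 33/0.80 = 41.25, rounded up to 42. Check: 42 × 0.80 = 33.6, which meets 33.

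**3. What 40 delivers.** 40 × 0.80 = 32, one short. The loss that 40 can absorb is 1 − 33/40 = 17.5%. If each patient independently completes with probability 0.80 (assumption), the chance that at least 33 of 40 complete is about 44%.

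**4. Cost in power.** Because the test is not specified, I set power to exactly 80% at N = 33 and recomputed at N = 32 (noncentral F or t, noncentrality f² × N).

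| Assumed test | f² giving 80% at 33 | Power at 32 |
|---|---|---|
| Single coefficient, two-sided, 1–10 predictors | 0.253–0.260 | 78.6–78.7% |
| Single coefficient, one-sided, 1–10 predictors | 0.196–0.200 | 78.8–78.9% |
| Overall R² test, 1, 2 or 3 predictors | 0.253, 0.323, 0.378 | 78.7%, 78.5%, 78.4% |

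The loss is therefore 1 to 2 percentage points. If 33 was rounded up from a fraction, the loss is measured from slightly above 80%, so power at 32 lies nearer to 80%. It is still below 80% wherever 33 is the smallest adequate N.

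**5. Can the 33 be checked?** Not from what is stated. At least two settings return exactly 33:

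- a one-sided single-coefficient test with f² = 0.20;
- a test of two terms among 11–14 predictors with f² = 0.35.

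Other settings do not. With f² = 0.15, a two-sided single coefficient needs 55. The 33 is unexplained, but it is not refuted.

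**6. What about 32 completers can detect** (two-sided alpha 0.05, 80% power). The design is an assumption in every row.

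| Assumed primary comparison | Detectable effect |
|---|---|
| Within-person change, 32 pairs | 0.51 SD of the change |
| Two arms of 16, unadjusted | 1.02 SD |
| Two arms of 16, baseline-adjusted, r = 0.5 | 1.02 × √(1 − 0.25) = 0.89 SD |
| Two arms of 16, baseline-adjusted, r = 0.6 | 1.02 × √(1 − 0.36) = 0.82 SD |

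The expected 95% confidence half-width is 2.04 × √(2/16) = 0.72 SD between two arms of 16. For a within-person change in 32 patients it is 2.04/√32 = 0.36 SD of the change. The detectable effect thus varies about twofold with a design choice that the power statement does not name.

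**The case against.** Four points can be made for the plan.

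- **The dropout slip is trivial.** It amounts to two enrolled patients, one completer and 1 to 2 points of power, and the 20% is itself only a planning guess. This stands as to size. It does not make 40 the right result of the stated inputs.
- **A condensed article may leave out effect size and predictor count.** This also stands, and their absence alone is not held against the plan. What remains lies in the printed text: a calculation declared not possible and then reported, with a power figure not linked to the primary objective.
- **Regression is a planned method, so the calculation may include the intervention term.** It may. The article does not say so, and a reader cannot assume it.
- **Calling the study exploratory already warns against a confirmatory reading.** In part. The warning is undercut a few lines later by an unqualified 80%.

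A stronger reading is tempting: that 33 cases imply a very large intervention effect, about 1 SD, and that the sample size is wrong at its base. The documents do not support it. The 1 SD figure needs a two-sided test of a single treatment coefficient, two roughly equal arms and no baseline adjustment, and the article states none of these. Its description of the comparison, measures before against measures after the intervention, can equally be read as within-person, where the detectable standardised change is about 0.5. A test left unspecified cannot imply one particular effect.

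**Conclusion.** The point holds in a limited form, and its severity is minor to moderate.

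- **Definite, from the article's own figures:** the minimum should be 42, not 40. At the stated dropout, 40 leaves 32 completers.
- **Small in effect:** power is about 78–79%, assuming that the unstated test has 80% at 33.
- **Definite, from the text:** the section contradicts itself on whether a formal calculation was possible, and it does not tie the 80% to the intervention effect named in the primary objective.
- **Not shown:** that 33 is wrong, or that it corresponds to any single effect size.

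The detectable effects of about 0.5 to 1.0 SD are conditional on the assumed designs. The Specifications table gives 400 patients; that is a separate inconsistency and plays no part here.

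**What to change.** 1. **Correct the dropout step.** State the minimum as 42 (33/0.80), or keep 40 and state that it tolerates 17.5% dropout.
2. **Remove the contradiction and qualify the power.** Choose one of two routes.
   - Drop the unqualified 80%, describe the study as exploratory, and give its expected precision for the named design: a 95% half-width of about 0.7 SD between two arms of 16, or about 0.36 SD of the change for a within-person comparison in 32 patients.
   - Keep a power statement, name the primary comparison, and state what about 32 completers can detect with 80% power: about 0.5 standardised change within person; about 1.0 SD for two equal arms unadjusted; or about 0.8–0.9 SD for two equal arms adjusted for baseline, with the assumed correlation (0.5–0.6) stated. If 42 are enrolled, rework these for 33 completers; they barely move.
3. **If the 33 is retained,** say which regression term it refers to and whether that term is the intervention effect.

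The cost is a few sentences of text, plus two more patients only if the sponsor prefers 42. No change to the analysis is needed.
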